## Methods

This is a double-blind randomised controlled trial protocol for examining the effectiveness of anthocyanins alone, and in combination with a multi-strain probiotic, over 3 months for adults aged ≥18 years with UC. One hundred eligible participants will be randomly assigned to one of four intervention arms in a 1:1:1:1 ratio for a 3-month duration: (1) 310 mg of anthocyanin derived from New Zealand blackcurrants with a placebo probiotic; (2) multi-strain probiotic with a placebo fruit powder; (3) 310 mg anthocyanin plus a multi-strain probiotic; (4) double placebo. Written informed consent will be obtained from all participants prior to commencing the trial.

### Recruitment

Participants will be recruited from across Australia, utilising gastroenterology and research networks. Additionally, social media advertising will be utilised to allow interested participants to contact the co-ordinating researcher. Recruitment will remain open until the sample size is met.

#### Sample size and power calculations

Our sample size (*n* 100) was calculated in G*Power Version 3.1.9.6 based on the primary outcome measure of a clinically relevant change in mean score of ≥16 in the 32-item Inflammatory Bowel Disease Questionnaire (IBDQ-32).^(39,40)^ The primary comparison of interest is between the combined intervention versus control. Assuming a mean change in the IBDQ-32 score of 16 ± 20 estimated from previous literature,^(41–44)^ α- significance of 0⋅05 and power 95 %, a sample size of n 19 per arm is required with effect size of 0⋅8. To allow for ~25 % drop-out, given the duration of this trial and based on previous literature,^(45–47)^
*n* 25 participants will be recruited to each arm.

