### Statistical analysis

Statistical analyses will be performed in Stata software,^(65)^ R software^(66)^ and/or IBM SPSS Statistics.^(67)^ An ITT analysis will be the primary analysis, including all participants randomised and analysed according to the treatment group to which they were originally assigned. A per-protocol analysis will additionally be conducted for all outcomes and used as a sensitivity analysis compared to the ITT. The per-protocol analysis will include participants who completed the trial without major violation including medical disruptions or unblinding, and who exhibited >80 % compliance to the intervention products.

Baseline demographics and measurements will be reported for each intervention group as means and standard deviations or 95 % CI.

The primary outcome will be the mean IBDQ-32 score at week 12 adjusted for baseline and covariates and assessed using an ANCOVA. A sensitivity analysis of differences in within-group change in IBDQ-32 score from baseline to week 12 will be measured using a two-sample *t*-test or Mann–Whitney *U*-test depending on normality of distribution. Within-group differences in secondary outcomes measured at two timepoints will be evaluated using a two-sample *t*-test or Mann–Whitney *U*-test depending on normality of distribution. Within-group differences in secondary outcomes measured at three time points will be evaluated using linear mixed modelling. Between-group differences of outcomes will be explored using ANOVA or ANCOVA if covariates need to be considered or mixed models. Relevant covariates associated with the primary outcome of health-related quality-of- life will be included in the analyses. Secondary analyses will be conducted to investigate relationships between changes in outcome measures. Predictors and assumptions of missing data will be investigated. Methods such as multiple imputation will be considered depending on the data missing. Appropriate sensitivity analyses will be performed.

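### The stated 95% power at 19 per arm is not the power of combined intervention versus control; for that comparison it is about 67% unadjusted and about 75–80% with baseline-adjusted ANCOVA

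*Protocol article*

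**What the plan says.** Under Sample size and power calculations, the Protocol article reports that the sample size "was calculated in G*Power Version 3.1.9.6" and identifies the contrast being sized: "The primary comparison of interest is between the combined intervention versus control". The inputs follow in one sentence: "Assuming a mean change in the IBDQ-32 score of 16 ± 20 estimated from previous literature", "α- significance of 0⋅05" and power of 95%, with the result that "a sample size of n 19 per arm is required with effect size of" 0.8. Allowing for about 25% drop-out, this becomes 25 recruited per arm, or 100 over four equally sized arms.

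The section does not name the test or say whether it is one- or two-sided, and it gives no correlation between baseline and follow-up scores.

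Under Statistical analysis, the primary analysis is also a comparison between arms: "The primary outcome will be the mean IBDQ-32 score at week 12 adjusted for baseline and covariates and assessed using an ANCOVA". A two-sample test on the change score appears there only as a sensitivity analysis.

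**The concern.** An effect size of 0.8 with 95% power normally needs about 40 participants per group in a comparison of two independent groups. Nineteen per arm is less than half of that, so the figure does not look like the result for the contrast named just before it.

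This is the article's only power statement and its justification for n = 100. If it is taken at face value, a null result would be read as strong evidence against a 16-point benefit, with a one-in-twenty chance of having missed one. On the article's own inputs, that chance is about one in three for an unadjusted two-sided test and about one in five to one in four for the planned ANCOVA (correlations of 0.5 to 0.7 assumed).

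**Working it through.** **Inputs from the article:** difference 16, SD 20 (worded as attached to a mean change), d = 16/20 = 0.8, alpha 0.05, target power 95%, 19 evaluable per arm, 25 recruited per arm, four arms. **Assumed, because not stated:** sidedness (both shown) and the correlation r between baseline and week-12 scores.

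**Step 1. Where 19 can come from.** All powers are exact, from the noncentral t distribution.
- Paired or one-sample t-test: noncentrality d√n, n − 1 df. At n = 19 this is 0.8 × √19 = 3.487 on 18 df. One-sided power is 95.6% (94.6% at n = 18), so the minimum n is 19, which is the stated figure. Two-sided power at 19 is 90.9%, and the minimum n is 23.
- Four-group, three-visit repeated-measures ANOVA, between-group effect, f = 0.4, with an assumed correlation of 0.5 between visits: λ = f² × N × m / (1 + (m − 1)ρ) = 0.16 × 76 × 3 / 2 = 18.24 on 3 and 72 df. Power is 95.1%, so this also gives 19 per arm. It is an omnibus test of four arms, not the named contrast.
- Plain one-way ANOVA does not give 19: f = 0.4 needs 42 per group (two groups) or 28 (four groups); f = 0.8 needs 12 or 8.

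**Step 2. The named comparison, unadjusted.** Two-sample t-test: noncentrality d√(n/2), 2n − 2 df. At n = 19: 0.8 × √9.5 = 2.466 on 36 df. At n = 25: 0.8 × √12.5 = 2.828 on 48 df.

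| | Two-sided | One-sided |
|---|---|---|
| Power, 19 per arm | 67.0% | 78.1% |
| Power, 25 per arm (no drop-out) | 79.1% | 87.4% |
| n per arm for 95% power | 42 | 35 |

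With 19 per arm and a two-sided test, the detectable difference is 18.7 points at 80% power and 24.0 points at 95% power.

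**Step 3. The planned ANCOVA.** If 20 is the SD of change and the score variance σ² is the same at both visits, then 400 = 2σ²(1 − r). The residual variance after baseline adjustment is σ²(1 − r²) = 200(1 + r).
- r = 0.5: residual SD √300 = 17.3
- r = 0.7: residual SD √340 = 18.4

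The noncentrality is 16 / (residual SD × √(2/n)). The error df, using all four arms, is 4n − 5, that is 71 at n = 19 and 95 at n = 25.

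| Assumed r | Noncentrality, n = 19 | Two-sided power, n = 19 | Noncentrality, n = 25 | Two-sided power, n = 25 |
|---|---|---|---|---|
| 0.5 | 2.85 | 80% | 3.27 | 90% |
| 0.7 | 2.67 | 75% | 3.07 | 86% |

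With the SD of change held at 20, power falls as r rises, because a high correlation means that the change score has already removed most of the baseline variation. At r = 0, two-sided power at 19 per arm is about 93%, still below 95%.

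**Step 4. Drop-out.** 25 × 0.75 = 18.75 and 19/0.75 = 25.3. The step from 19 to 25 is about right and is not part of the problem.

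**The case against.** **The primary analysis is ANCOVA, so 67% is not its power.** This stands. The 67% describes an unadjusted two-sided t-test and should not be quoted alone. The ANCOVA figures are higher but remain below 95% at 19 per arm for any non-negative correlation, two-sided. Participants who stop treatment are also encouraged to supply final outcome data, so the evaluable number may lie between 19 and 25. Power would then lie between the two columns of the ANCOVA table.

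**The test may have been meant as one-sided.** The article does not say. One-sided, the unadjusted power is 78% at 19 per arm and 87% at 25, which is a smaller shortfall.

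**20 might be the SD of the score rather than of the change.** ANCOVA at 19 per arm would then reach about 92% (r = 0.7) or 98% (r = 0.8) two-sided. The article attaches the 20 to a mean change and gives no correlation, so this is possible but not what it says. The cited sources are not available to settle it.

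**Two stronger readings go beyond the document.** A reader might infer that a one-sided within-arm test was definitely run. The match is exact, but the article does not name the test, and the repeated-measures calculation also gives 19. A reader might also infer that 16 is a within-arm change and that power is lower still once control-arm improvement is subtracted. The wording allows this, but the article does not say whether the value is within-arm or between-arm and gives no control-arm change, so any lower figure would rest on invented inputs.

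**Conclusion.** The power statement is wrong as written for the comparison to which it is attached. With a 16-point difference, SD of change 20 and alpha 0.05, combined intervention versus control at 19 per arm has 67% power two-sided (78% one-sided) unadjusted. With two-sided ANCOVA it has about 80% at r = 0.5 and about 75% at r = 0.7.

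The unadjusted figures use only the article's inputs plus a choice of sidedness. The ANCOVA figures also assume the correlations, equal variance at both visits and an error variance pooled over four arms. All take 16 as the true between-arm difference. How 19 was obtained remains unknown, and the conclusion does not depend on it. The finding does not show that n = 100 is unacceptable, only that its stated justification does not hold.

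**What to change.** Keep n = 100 and delete the 95% claim. State that the test is two-sided and that 16 points is a between-arm difference, net of any change in the control arm. Replacement text could read:

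> *With 19 completers per arm, the two-sided 5% comparison of the combined intervention with double placebo has 67% power, unadjusted, for a between-arm difference of 16 points (SD of change 20). With baseline-adjusted ANCOVA, power is about 80% if the baseline correlation is 0.5 and about 75% if it is 0.7. The difference detectable with 80% power without adjustment is 18.7 points.*

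Each correlation should stay paired with its own power, because a bare range of 75–80% for 0.5–0.7 would suggest that power rises with correlation.

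The cost is a change of wording in the protocol, and in the registry entry if it repeats the claim, with a less favourable stated power. No more patients are needed.

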### Inclusion and exclusion criteria

Inclusion criteria: (1) diagnosis of UC for at least 3 months prior to screening, documented by endoscopic and histologic findings; (2) aged ≥18 years; (3) willing and able to take oral supplements; (4) able to communicate in the English language.

Exclusion criteria: (1) CD; (2) change in antibiotics or probiotics in past 3 months, including commencing antibiotics/probiotics, ceasing antibiotics/probiotics or changing the type of antibiotic/probiotic consumed; (3) escalation to biologics or immunomodulators in the past 6 weeks; (4) currently taking steroids >20 mg daily; (5) bowel resection surgery; (6) pregnant and lactating women; (7) end-stage liver or kidney failure; (8) current treatment for *Clostridium difficile* or other intestinal infection; (9) sucrose-isomaltose deficiency or maltose intolerance.

As per the Medical Advisor's recommendation, all participants must have stable medication for 2 weeks prior to commencing the study. All types of IBD medications are permitted in this study. Participants who have taken antibiotics or probiotics consistently for 3 months prior to recruitment will be permitted to commence the study, provided they agree to continue taking the probiotic/antibiotics throughout the study. Patients receiving topical therapy (enemas or suppositories) are eligible to participate if they are willing to continue the therapy at a stable dose throughout the study. Participant receiving steroids >20 g/day can commence the study 2 weeks after their dosage has reduced to ≤20 mg/day. Participants treated with steroids ≤20 mg/day are eligible to participate if they plan to maintain this stable dose for all the study duration.

Participants who require a change in their medication treatment related to uncontrolled UC activity (i.e. increase in steroids or mesalamine doses, start of steroids or biologics or immunosuppressants) during the 12-week intervention, those who do not comply with the study protocol, and those who voluntarily leave the study will not be included in the per-protocol analyses. These participants will be encouraged to continue to complete required outcome data and attend the final visit for inclusion in the intention-to-treat (ITT) analysis.

### Screening procedure

All interested participants will complete a screening survey covering all aspects of the inclusion and exclusion criteria. If eligible, participants will be contacted by the researchers and sent a participant information sheet and consent form. A baseline appointment will then be scheduled.

### Randomisation and allocation concealment

Participants will be block randomised upon enrolment into one of four categories by a single researcher who will not be involved in data collection, and who will organise the corresponding active or placebo products for each participant. For blinding purposes, the code allocation will be concealed and known only to this researcher until statistical analysis has been completed. In the case that unblinding is required for medical reasons or adverse reactions, the researcher responsible for randomisation will reveal the product allocation to the participant. If the participant continues in the study, their results will be included in the ITT analysis but excluded from per-protocol due to unblinding. A Consolidated Standards of Reporting Trials (CONSORT) flow chart outlining the study schedule is displayed in Fig. 1.

**Fig. 1. fig01:**
[figure not shown]
Consolidated standards of reporting trial flow diagram of the study schedule.

### Interventions

#### Anthocyanin intervention

12 g of freeze-dried New Zealand blackcurrant powder (Arepa Neuroberry®) provided by Arepa Holdings will be consumed daily by participants in intervention arms 1 and 2. This provides 310 mg of anthocyanins/day. The product can be mixed in any cold, low acidity, non-carbonated drink, or food (i.e. smoothie, juice, water, milk or on yoghurt or cereal). Previous research has shown no statistically significant adverse reactions or harm associated with polyphenol interventions in adults with IBD.^(37)^

#### Probiotic intervention

Participants in intervention arms 2 and 3 will receive the multi-strain probiotic VSL#3® supplied by Actial Farmaceutica, in the form of two daily sachets. This probiotic contains one strain of *Streptococcus thermophilus* BT01, three strains of Bifidobacteria (*B. breve* BB02; *B. animalis* subspecies [subsp] *lactis* BL03, previously identified as *B. longum* BL03; and *B. animalis* subsp. *lactis* BI04, previously identified as *B. infantis* BI04), and four strains of Lactobacilli (*L. acidophilus* BA05, *L. plantarum* BP06, *L. paracasei* BP07, and *L. helveticus* BD08, previously identified as *L. delbrueckii* subsp. *bulgaricus* BD08). VSL#3® contains no less than 450 billion colony-forming units (CFUs) per single sachet. The product can be mixed in any cold, low acidity, non-carbonated drink or food (i.e. smoothie, juice, water, milk, or on yoghurt or cereal). Probiotic interventions in adults with IBD have shown a risk of abdominal pain and other gastrointestinal side effects such nausea, abdominal cramping and flatulence. No other harms associated with probiotic interventions in this population group have been documented.^(48)^

#### Placebo

Participants in intervention arms 3 and 4 will receive 12 g of a placebo powdered fruit extract with texture and taste matched to the blackcurrant powder. Participants in intervention arms 1 and 4 will receive two placebo sachets of similar appearance to the provided probiotic.

### Outcome measures

See Table 1 for the timeline of outcome measures.

**Table 1. tab01:** Data collection schedule for four study arms

Outcomes	Measure/Method	1st Interview	6 weeks	2nd Interview	Early termination interview
Anthropometry	Self-reported height and weight	X		X	X
Clinical	Inflammatory Bowel Disease Questionnaire	X	X	X	X
	Inflammatory Bowel Disease Symptom Inventory – Short Form	X	X	X	X
	Bristol Stool Chart	X		X	
	Shotgun metagenomic sequencing of faecal sample	X		X	
	Faecal Calprotectin	X		X	
	Three non-consecutive 24 h dietary recall	X	X	X	
Lifestyle and medical history	Demographic survey	X			
	Medications and IBD clinical history	X			X
	SCCAI	X		X	X
Cognitive performance, mood, and attention	DASS-21 questionnaire	X		X	
	Stroop test	X		X	
	RAVLT	X		X	

#### Health-related quality of life (HRQOL)

The primary outcome of HRQOL will be measured using the IBDQ-32. The IBDQ-32 is a validated 32-item self-reported questionnaire, assessing quality of life (QOL) across four disease-specific sub-categories: bowel symptoms (ten questions); systemic symptoms including sleep disorders and fatigue (five questions); emotional function (twelve questions); and social function (five questions).^(49)^ The total score ranges from 32 to 224 points, with lower scores reflecting lower HRQOL. Each question is scored using a 7-point Likert scale ranging from 1 (low QOL) to 7 (high QOL). All participants will complete the IBDQ-32 at baseline, 6 weeks, and 12 weeks. The change in total IBDQ-32 score has been demonstrated to detect, with reliability and sensitivity, changes in disease activity and endoscopic mucosal healing in response to treatment.^(40,50,51)^ A change in total score of ≥16 points has been shown to correlate to a clinically meaningful change in QOL.^(39,40)^

#### Secondary outcome measures

Shotgun metagenomic sequencing of faecal microbiota samples will be performed at baseline and 12 weeks, to profile the taxonomic composition and functional potential of all microbial communities present in the faecal microbiota.^(52)^ This sequencing will capture any changes to the composition and functional potential of the faecal microbiota after the intervention.

Faecal samples collected for shotgun metagenomic sequencing will be collected in commercial faecal kits from Microba Life Sciences. The Microba commercial kit includes a Copan FLOQSwab in an active drying tube that has been tested to preserve samples at room temperature for up to 10 weeks. Samples will be sent via post to Microba Life Sciences and will be stored at −80 °C until all samples are collected. Metagenomic sample processing and sequencing will be performed at Microba Life Sciences. Faecal samples will be extracted using the DNeasy 96 PowerSoil Pro QIAcube HT Kit (Qiagen 47021) in 2-ml deep well plate format as per manufacturer's instructions with a modified initial processing step on the QIAcube HT DNA extraction system (Qiagen 9001793). Libraries will be constructed using the Illumina DNA Prep (M) Tagmentation Kit (Illumina, 20018705) with IDT for Illumina DNA/RNA UD Index Sets A-D (Illumina 20027213-16) according to manufacturer's instructions, with a modification of volume to accommodate processing in a 384-plate format. Resulting libraries will be assessed using a high sensitivity dsDNA fluorometric assay (QuantIT, ThermoFisher, Q33120) and individual libraries are visualised with capillary gel electrophoresis using the QIAxcel DNA High Resolution Kit (Qiagen, 929002). Individual libraries will be pooled in equimolar amounts to create a sequencing pool which is assessed using a high sensitivity dsDNA fluorometric assay (QuantIT, ThermoFisher, Q33120) and will be visualised with capillary gel electrophoresis using the QIAxcel DNA High Resolution Kit (Qiagen, 929002). Sequencing pools will then be loaded and sequenced on the NovaSeq6000 (Illumina) using v1.5 300 bp PE sequencing reagents, according to the manufacturer's instructions. Metagenomic sequencing data quality control will be performed at Microba Life Sciences. Paired-end DNA sequencing data will be demultiplexed and adaptor trimmed using Illumina BaseSpace Bcl2fastq2 (v2.20) accepting one mismatch in index sequences. Reads will then be quality trimmed and residual adaptors removed using the software Trimmomatic v0.39^(53)^ with the following parameters: -phred33 LEADING:3 TRAILING:3 SLIDINGWINDOW:4:15 CROP:100000 HEADCROP:0 MINLEN:100. All samples will then be randomly subsampled to a standard depth of seven million read pairs.

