### Research aim and objectives

This study aims to evaluate the combined effect and clinical significance of a multi-strain probiotic intervention (VSL#3®^,^ containing one strain of *Streptococcus thermophilus*, three strains of *Bifidobacterium* and four strains of *Lactobacillus*) provided together with dietary anthocyanins extracted from New Zealand-grown blackcurrants on the gut microbiota profile and inflammatory biomarkers in adults with UC.

We hypothesise that (1) anthocyanins, in combination with probiotics, will result in a reduction in gut inflammation measured by faecal calprotectin (FCAL) and will modulate the gut microbiome measured through shotgun metagenomic sequencing of faecal samples; (2) anthocyanins, in combination with probiotics, will result in a synergistic effect that results in a significantly greater reduction in FCAL and improvement in the gut microbiome than each intervention alone; (3) the reduction in FCAL will be explained by beneficial changes to the gut microbiome profile; and (4) these changes in FCAL and the gut microbiome will lead to clinically significant improvements in health-related quality-of-life measured with the IBDQ-32.

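### Stool sequenced at the end of dosing does not separate the administered probiotic strains from a change in the resident gut microbiota (minor)

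*Protocol article*

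**What the plan says.** **Dosing.** The section Probiotic intervention states: "Participants in intervention arms 2 and 3 will receive the multi-strain probiotic". The product is supplied "in the form of two daily sachets" and "contains no less than 450 billion colony-forming units (CFUs) per single sachet". It names eight strains. The sections on the interventions and the placebo disagree with the opening of Methods on whether arm 2 or arm 3 is the combined arm. Both are probiotic arms under either numbering, so the arms are named by content here.

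**Sampling.** Inclusion and exclusion criteria gives the length of treatment ("during the 12-week intervention"). Secondary outcome measures states: "Shotgun metagenomic sequencing of faecal microbiota samples will be performed at baseline and 12 weeks". Table 1 shows the same two time points and no later stool sample.

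**Outcome and hypotheses.** Secondary outcome measures says of the assay: "This sequencing will capture any changes to the composition and functional potential of the faecal microbiota after the intervention". On processing it adds: "All samples will then be randomly subsampled to a standard depth of seven million read pairs". In Research aim and objectives, hypothesis 1 says the combination "will modulate the gut microbiome measured through shotgun metagenomic sequencing of faecal samples", with no direction and no taxa named; it also predicts a fall in FCAL. Hypothesis 2 expects the combination to improve the microbiome more than either product alone. Hypothesis 3 expects beneficial microbiome changes to account for the FCAL reduction.

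**The concern.** Shotgun sequencing reads whatever bacterial DNA is in the stool, including DNA from organisms swallowed as treatment. The follow-up sample falls at the end of dosing, so two different things enter the same measurement: the product in transit and a response of the resident community.

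The trial's own rationale makes the distinction matter. The Introduction describes a cross-feeding mechanism in which *Bifidobacterium* and *Lactobacillus* support butyrate-producing bacteria, and it says those producers cannot yet be given as a supplement. The response of most interest is therefore in organisms outside the sachet. The Introduction also cites a meta-analysis in which probiotics of this kind raised the two dosed genera in participants' stool, so the article's own evidence leads one to expect a product signal.

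At stake is what a positive microbiome result would mean. A difference between probiotic and non-probiotic arms could be reported as modulation when it shows only that participants took the product.

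**Working it through.** The plan gives no figure for the microbiome outcomes, so there is none to reproduce. The check has three parts.

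**1. How much product, and how many taxa**

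- Daily dose: 2 sachets × 450×10⁹ CFU = 9×10¹¹ CFU, as a minimum.
- Species listed in Probiotic intervention: *S. thermophilus*, *B. breve*, *B. animalis* subsp. *lactis* (two strains), *L. acidophilus*, *L. plantarum*, *L. paracasei*, *L. helveticus*. That is seven species from eight strains.
- Observed richness could rise by at most 7 from the product alone, and only if all seven species were absent at baseline.

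**2. How many reads the product could contribute**

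By assumed abundance of one administered species: read pairs = 7,000,000 × abundance.

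- 0.01%: 700
- 0.1%: 7,000
- 1%: 70,000

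If all seven species sat at the same level, their total share would be 7 × 0.01% = 0.07% to 7 × 1% = 7%. At a fixed depth, resident reads fall by that share, which is why the filtered data need renormalising.

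By assumed recovery, for all dosed strains together: read pairs = 7,000,000 × D·r / (T + D·r). Here D = 9×10¹¹ per day, r is the fraction recovered in stool and T is daily faecal bacteria. Reads are taken as proportional to cells. Neither r nor T is in the documents.

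| Assumed r | T = 10¹² | T = 10¹³ | T = 10¹⁴ |
|---|---|---|---|
| 10% | 577,982 | 62,438 | 6,294 |
| 1% | 62,438 | 6,294 | 630 |
| 0.1% | 6,294 | 630 | 63 |
| 0.01% | 630 | 63 | 6 |
| 0.001% | 63 | 6 | 1 |

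Over most of this range the product leaves a readable trace. At the low end it may not.

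Whether a trace becomes a difference between arms depends on background carriage. The calculation uses the plan's 19 evaluable per arm, a two-sided 5% level, and power = Φ{[|p₁−p₀| − 1.96·√(2p̄(1−p̄)/n)] / √([p₁(1−p₁)+p₀(1−p₀)]/n)}. All detection rates are assumed.

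- 70% versus 5%: (0.65 − 1.96×0.157)/0.116 = 2.94, power 99.8%
- 70% versus 30%: (0.40 − 1.96×0.162)/0.149 = 0.55, power 71%
- 50% versus 30%: (0.20 − 1.96×0.159)/0.156 = −0.72, power 24%

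Background carriage is a real possibility, because Inclusion and exclusion criteria lets participants in any arm continue a probiotic they already take.

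**3. Which hypotheses are exposed**

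| Comparison | Product on one side only? | Consequence |
|---|---|---|
| Hypothesis 1, microbiome part, combined vs double placebo | Yes | Product can be read as modulation |
| Hypothesis 1, FCAL part | Not a sequencing measure | Unaffected |
| Hypothesis 2, combined vs anthocyanin alone | Yes | Product can be read as improvement |
| Hypothesis 2, combined vs probiotic alone | No, same product in both | Largely protected |
| Hypothesis 3, microbiome change explaining FCAL | Product reads mark arm and adherence | Can be confounded |

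On hypothesis 3: if a probiotic arm lowers FCAL by any route, product reads will track FCAL across arms whether or not resident taxa changed.

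**The case against.** The strongest reply is that handling reads from dosed strains is an analysis detail, and a condensed article may leave it to a full protocol or SAP that is not shown. That stands as far as the missing filtering step goes: its absence is not the fault here. What remains is what the article does fix, namely stool sampled only at baseline and at the end of dosing, and a first hypothesis that any compositional change could satisfy. If an SAP already separates the dosed taxa, one sentence in the article would reconcile the two.

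A second reply is that the sentence about capturing any changes describes what the assay can see and is not a rule for success. That is right, and a reader who infers such a rule goes beyond the text. Hypotheses 2 and 3 also use narrower terms, improvement and benefit. Hypothesis 1 does not.

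A third reply concerns the remedy. The dosed genera are the proposed mediators. If anthocyanins help the dosed strains persist, that would itself be the synergy sought in hypothesis 2, and an analysis that simply deleted those species would hide it. This stands. It rules out making filtered data the only main analysis, but it does not argue against reporting both.

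**Conclusion.** The concern holds in limited form. As written, the administered strains and their genes can be read as modulation in probiotic versus non-probiotic comparisons. The microbiome part of hypothesis 1 and one of the two contrasts in hypothesis 2 are exposed, and hypothesis 3 is open to confounding.

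A reader might infer that a positive microbiome result is all but assured and that hypotheses 1 to 3 go untested. The documents do not support that. They give neither faecal recovery nor bacterial load, and the assumed ranges run from about 1 read pair to several hundred thousand. Detecting a strain is also not the same as a significant difference in diversity or function. The FCAL part of hypothesis 1 is untouched, combined versus probiotic alone carries the same product on both sides, and hypothesis 3 needs an association with FCAL that detection alone does not create. Taxa outside the product remain testable throughout.

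The conclusion assumes that the week-12 stool is collected during product intake or soon after it ends, which the two-visit schedule implies but does not state. Severity is minor: the microbiome is a secondary outcome, and the IBDQ-32 analysis and sample size are not affected.

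**What to change.** Before unblinding, add to Secondary outcome measures and Statistical analysis:

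- Composition, diversity and functional-potential results are reported twice: for all taxa, and after removing the seven administered species (or the eight strains, if they can be resolved) and renormalising.
- A claim that the resident microbiome changed, under hypothesis 1 or 2, must be supported by the non-administered taxa. So must the test in hypothesis 3 that microbiome change explains the FCAL change.
- Administered taxa are reported separately as exposure or engraftment, including combined versus probiotic alone, so that a prebiotic effect of anthocyanins on the dosed strains stays visible.

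The cost is one additional analysis of data the trial already plans to generate, with no new samples or visits. The drawback is that species-level filtering also removes resident members of those seven species; the all-taxa analysis, reported alongside, covers this.
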